## Assignment of interventions: allocation

### Sequence generation {16a}

Eligible care homes will be randomised (via the North Wales Organisation for Randomised Trials in Health [NWORTH]) based on a 1:1 ratio (20 intervention and 20 control). Stratification of care homes will be based on care home site (England, Northern Ireland, Wales) and care home size (based on number of available beds within the care home: small 1–10 beds; medium 11–49 beds; large 50 +). NWORTH’s dynamic adaptive algorithm [53] will be used to balance these factors a priori, and these factors will be adjusted for post hoc as part of the analysis.

### Concealment mechanism {16b}

Local study team members will allocate the care homes using a dynamic adaptive randomisation algorithm [53].

### Implementation {16c}

Since this is a cluster RCT, residents will be allocated to the treatment that have been assigned to the care home. An independent NWORTH member of staff will allocate the care homes and a member of the local study team will enrol residents on to the study.

## Assignment of interventions: blinding

### Who will be blinded {17a}

It is not possible to blind the care homes, the individual residents in the trial or outcome assessors, but the trial statistician will remain blind throughout the duration of the study, until the blinded analysis detailed in the statistical analysis plan has been conducted and reported to the study team.

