There is increasing evidence that Dental Care Professionals (DCPs) offer an alternative to using dentists to meet the future challenges in dental public health [18, 19]. DCPs are a broad range of professionals, which include dental therapists (DTs) and dental nurses (DNs). Previous research has demonstrated that DTs can identify and screen for dental caries and periodontal disease and are safe as front-line health care workers [20–22]. The feasibility, productivity and effectiveness of using DTs has been tested in primary care [21, 23, 24], but little has been undertaken in a care home environment. Emerging evidence suggests that the use of DCPs (DTs and DNs) within care homes has the potential to improve preventive advice, the provision of care and access to services [25].

Following a retrospective analysis of the 2010 Welsh dental care home survey data, Monaghan & Morgan [26] concluded ‘a large proportion of need in care homes could be wholly provided by hygienists or therapists’ and an ‘efficiency gain of direct access arises from individuals who do not need to see a dentist for any aspects of their care’. It is also argued that DTs can lead examinations in care home settings [27]. However, robust empirical evidence from definitive trials about how best to successfully implement and sustain DCP interventions within care home environments is currently lacking.

The aim of this study is to determine whether DCPs could reduce plaque levels (improve the oral cleanliness) of dentate older adults (over 65 years of age) residing in care homes over a 6-month period, when compared to ‘treatment as usual’ (commonly a reactive and ad hoc service provided by dentists), and also to determine whether this effect is sustainable over a further 6-month follow-up period.

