## Methods: participants, interventions and outcomes

### Study setting {9}

The trial will be conducted in 40 care homes from across Wales, Northern Ireland and England (London and North England). Further information about recruitment and randomisation of care homes is presented in the relevant sections below. DTs and DNs employed by the Community Dental Service (CDS) in each region will deliver the oral health intervention. CDSs are charged with the responsibility of providing NHS service provision for care homes on a regional basis.

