### Outcomes {12}

#### Primary outcome in the trial

The Primary Outcome Measure (POM) for this study will be the Silness-Loë Plaque Index [42]. The index is a 4-point scale (measuring the amount of dental plaque present on six index teeth) ranging from 0-no plaque to 3-abundance of dental plaque within the gingival pocket and/or on the tooth and gingival margin. In accordance with the index, the mean will be calculated from these ordinal scores on the six index teeth. The prevailing model in the dental literature is to measure the change in this mean score. However, this model is difficult to infer clinical significance at a population level. To this end, the proportion of individuals in each arm that have demonstrated a 50% reduction in their mean Silness-Loë Plaque Index from baseline will be calculated. This will enable the change in the mean plaque index at the individual level to be measured, whilst providing a meaningful primary outcome measure at a population level.

The sample size calculation (see section ‘Sample size {14}’) is based and powered on changes to the POM at 6 months. This takes account of the ‘time-to-effect’ of the intervention on the POM and the pragmatic consideration of the length of stay of eligible residents. However, a follow-up at 12 months will be undertaken to determine whether the effect seen at 6 months can be sustained. This aligns with the eligibility criteria and the estimated length of stay that the residents have in a care home [43].

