#### Clinical outcomes

Clinical outcomes include the degree of dental plaque present (POM) assessed by Silness-Loë Plaque Index [42]), number of new carious lesions (coronal and root caries) and episodes of bleeding on probing on six index teeth. The dental examination will be undertaken at baseline, 6 months and 12 months by trained dental examiners from the CDS at each study site (CDS organisations are large enough to prevent contamination between measurements of clinical indices and the delivery of the intervention). The dental examination will be undertaken on six index teeth (according to Ramfjord) to reduce the burden on participating residents [44].

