### Frequency and plans for auditing trial conduct {23}

A monitoring plan, based on a risk assessment, will be prepared prior to participant recruitment detailing the monitoring strategy for the trial. The plan will include procedures for day-to-day centralised monitoring, process for setting the 6- and 12-month follow-up assessments conducted by DCPs, the requirements for source data verification, Investigator Site File audit, and for identification of protocol deviations and serious breaches of protocol and/or GCP.

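### Blinding of outcome assessors is ruled out without a reason, although separate examiners are already planned, and it is left unclear who scores the primary outcome at follow-up

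*Protocol article*

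**What the plan says.** Four places in the protocol article bear on the point.

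- **Who will be blinded {17a}:** "It is not possible to blind the care homes, the individual residents in the trial or outcome assessors". No reason is given. The only blinded role is the analyst: "the trial statistician will remain blind throughout the duration of the study".
- **Clinical outcomes** (under Plans for assessment and collection of outcomes {18a}): "The dental examination will be undertaken at baseline, 6 months and 12 months by trained dental examiners from the CDS at each study site". The same sentence adds that "CDS organisations are large enough to prevent contamination between measurements of clinical indices and the delivery of the intervention".
- **Frequency and plans for auditing trial conduct {23}:** the monitoring plan is to cover the "process for setting the 6- and 12-month follow-up assessments conducted by DCPs". The background section says that "DCPs are a broad range of professionals, which include dental therapists (DTs) and dental nurses (DNs", and Study setting {9} says that "DTs and DNs employed by the Community Dental Service (CDS) in each region will deliver the oral health intervention".
- **Primary outcome in the trial:** "The index is a 4-point scale (measuring the amount of dental plaque present on six index teeth". It is scored 0 to 3 and averaged over the six teeth. A resident counts as a success if that mean has fallen by 50% from baseline at 6 months.

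The participant timeline also places allocation of homes before residents are selected, consented and assessed at baseline.

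**The concern.** When an outcome is scored by eye, keeping the scorer unaware of allocation is the main protection against differential scoring. The article gives up that protection in one clause, without argument, while describing staffing that would make an attempt possible. It also leaves open whether those who score at follow-up could come from the professions that deliver the intervention.

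The endpoint raises the stakes. Success requires crossing a threshold on a mean of six ordinal scores, and one grade on one tooth moves that mean by 1/6 = 0.167. A slight tendency to score lower in one arm can therefore carry residents over the line. Because allocation comes before baseline, both ends of the percentage fall are exposed. Neither the planned multi-level model nor multiple imputation can remove a bias that sits in the recorded scores.

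**Working it through.** **Step 1. Set the statements side by side.**

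- The blinding section says assessors cannot be blinded. The clinical-outcomes section says measurement is organisationally separate from delivery. Separation is not masking, so the two can both be true. But staff who take no part in delivery can be kept uninformed of a home's arm. What the article supports is that masking cannot be assured, not that it is impossible.
- The clinical-outcomes section names CDS examiners without stating their profession. The auditing section says DCPs. DCPs include therapists and nurses, and CDS therapists and nurses deliver the intervention. An examiner could be a DCP who delivers nothing in this trial, so the two statements are ambiguous against each other rather than contradictory.

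**Step 2. Reproduce the planned design**, to obtain the precision used below. Inputs from Sample size {14}: 20 homes per arm, 5 completers per home, ICC 0.05, proportions 0.10 and 0.29, 5% significance (taken as two-sided), attrition 28%.

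- Design effect = 1 + (5 − 1) × 0.05 = 1.20. Effective n per arm = 100 / 1.20 = 83.3.
- SE = √[(0.10 × 0.90 + 0.29 × 0.71) / 83.3] = 0.0596.
- Power = Φ(0.19 / 0.0596 − 1.96) = Φ(1.23) = 0.89, against the stated 0.90 (0.88 with a pooled variance).
- Total = 200 / 0.72 = 278, against the stated 280.

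The design reproduces closely, and no number in it is disputed here.

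**Step 3. Sensitivity to differential scoring.** The documents give no SD, no correlation and no size of bias, so all of these are assumptions: baseline mean 1.6 or 2.3; SD 0.5 or 0.7; baseline-to-6-month correlation 0.3 or 0.5; scores limited to 0-3; control drift set so that 10% halve their score; no true effect; 6-month scores lowered by 0.1 or 0.2 in the intervention arm only. Success rates come from simulating 400,000 residents per setting.

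With d = p − 0.10 and SE = √[(0.09 + p(1 − p)) / 83.3], the false-positive rate is Φ(d/SE − 1.96) + Φ(−d/SE − 1.96). Example: p = 0.141 gives d = 0.041, SE = 0.0503 and d/SE = 0.81, so 0.126 + 0.003 = 0.13.

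| SD | Scored lower by | Success, intervention arm | False-positive rate |
|---|---|---|---|
| 0.5 | 0.1 | 14.1-14.7% | 13-15% |
| 0.5 | 0.2 | 19.1-20.7% | 39-49% |
| 0.7 | 0.1 | 12.8-13.2% | 9-10% |
| 0.7 | 0.2 | 16.1-17.1% | 22-27% |

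A cross-check that uses no plaque model (pooled variance) agrees in scale: 5 extra percentage points of apparent success in the intervention arm give a false-positive rate of 16%, and 10 points give 44%. The whole planned effect is 19 points.

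**Step 4. Bias at both visits.** If scores are lowered by s at baseline and at follow-up, success means f − s ≤ 0.5(b − s), that is f ≤ 0.5b + 0.5s. The net shift is halved. If baseline is instead scored higher by s, success means f ≤ 0.5b + 1.5s, and the shift grows by half. The documents do not settle which would apply.

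**The case against.** The strongest reply is that the article is being candid. Examinations take place in the home, and residents and staff know their arm. Intervention homes have repeated nurse visits, staff training and manuals on site, and examiners share an employer with the delivery staff. Some examiners will learn the allocation whatever the protocol says, and keeping measurement apart from delivery is already some mitigation. This stands as far as it goes: masking cannot be promised. It does not justify making no attempt.

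Three stronger readings are tempting and are not supported.

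- **That the sections flatly contradict each other, or that delivery staff will score their own work.** The auditing sentence describes the content of a future monitoring plan, and DCP is a broad term. The wording permits that reading but does not state it.
- **That the 6-month therapist visit coincides with the outcome examination, so plaque just removed counts as success.** The text fixes only how often therapists visit. The figure with the visit schedule is not available here, and no section says that the visit removes plaque. If it did, a masked examiner would record the same low score, so this is a question of outcome timing and not of detection bias.
- **That the trial will produce a false positive.** The figures depend on an assumed SD and an assumed leniency. They fall markedly at SD 0.7, and bias in the same direction at baseline would halve the shift.

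**Conclusion.** The concern holds in a limited form. The statement that assessors cannot be blinded is unjustified, because the article already plans examiners separate from delivery and masking could be attempted. The identity of the follow-up assessors is ambiguous between two sections and must be reconciled. The outcome is of a kind that small differential scoring can distort.

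The size of any bias cannot be derived from the documents. Under the stated assumptions (SD 0.5 to 0.7, no true effect, bias at follow-up only), the false-positive rate would be roughly 9-15% for a 0.1 shift and 22-49% for a 0.2 shift, against a nominal 5%. These figures show sensitivity and are not a forecast.

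This should be fixed, with moderate confidence. It does not invalidate the design.

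**What to change.** 1. **Who will be blinded {17a}:** say that homes and residents are not blinded, but that the CDS examiners who score the index are not told the home's allocation, take no part in delivering the intervention, and record at each examination whether they became aware of the arm.
2. **Frequency and plans for auditing trial conduct {23}:** replace the reference to DCPs with the examiners named under Clinical outcomes, and state that they are not delivery staff.
3. **Outcome timing, a separate point:** unless the schedule figure already fixes it, state that the 6-month outcome examination comes before any trial treatment by the therapist in that visit round. This concerns when the outcome is measured, not how residents are treated.

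The cost is protocol and training wording, one item on the examination form, and some care in booking visits. Separate examiners are already planned and the sample size does not change. Some examiners will still be unblinded by staff or residents, but this would be recorded and could be reported. The article describes the trial as not yet recruiting, so the change could be made before the first examination.

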### Procedure for unblinding if needed {17b}

The statistician will be unblinded to allocation after the statistical analysis plan has been conducted and reported to the study team.

## Data collection and management

### Plans for assessment and collection of outcomes {18a}

All study participants (intervention and control arms) will undergo a dental examination to collect clinical data and will complete pre-printed validated questionnaires and a symptom checklist to collect person-centred outcomes. The following assessments will take place at the care home for each recruited resident:

#### Clinical outcomes

Clinical outcomes include the degree of dental plaque present (POM) assessed by Silness-Loë Plaque Index [42]), number of new carious lesions (coronal and root caries) and episodes of bleeding on probing on six index teeth. The dental examination will be undertaken at baseline, 6 months and 12 months by trained dental examiners from the CDS at each study site (CDS organisations are large enough to prevent contamination between measurements of clinical indices and the delivery of the intervention). The dental examination will be undertaken on six index teeth (according to Ramfjord) to reduce the burden on participating residents [44].

#### Person-centred outcomes

HRQoL will be assessed through the EQ−5D−5L questionnaire [45]. This questionnaire will be administered by a trained member of the local study team to all participants at baseline, 6 months and 12 months;OHRQoL will be assessed using the OIDP questionnaire [46]. This questionnaire will be administered by a trained member of the local study team to all participants at baseline, 6 months and 12 months;Oral symptoms and episodes of unscheduled care. This refers to the number of reported episodes of dental pain, sepsis, discomfort and urgent dental care appointments. Care home staff using a checklist diary log will collect this information weekly; andThe number of onward referrals to dentists, when the treatment needed extends beyond the DTs’ Scope of Practice [33], will be collected weekly by care home staff, and by a member of the local study team at baseline, 6 months and 12 months.

#### Other information

On entry into the study, the local study team will complete a Six-item Cognitive Impairment Test (6-CIT) [30] with each resident in order to assess their level of cognitive function. In order to be as inclusive as possible, all residents that are able to provide consent will be included in the study, but a record will be kept of their 6-CIT scores: 0–7 = normal cognitive function; 8–9 = mild cognitive impairment; > 10 = severe cognitive impairment. The impact of this change to the eligibility criteria is reflected in the increase of our modelled attrition rate (28%). A sensitivity analysis will be undertaken at the analysis stage to determine its effect on the POM. A log will be kept of residents who decide not to participate and the number of residents who were unable to provide consent.

#### Cost-effectiveness data

Costs fall under a number of headings and will be gathered under these. Programme delivery costs (DN and DT) in terms of (i) staff time; (ii) travel costs; (iii) consumables (such as toothpaste) and (iv) production of training materials and websites will be collected using a combination of staff diaries and programme records. Staff time will be monetised using estimates of salary costs from published sources; travel time using costs per mile travelled and consumables based on programme acquisition costs. Production of training materials and development of the website will be treated as a fixed cost and based on programme records. Other dental costs will be based on a review of patient records with respect to dental care beyond preventive activities provided by DN and DT or other dental practitioners. This will be monetised using the Statement of Dental Remuneration for Northern Ireland, which provides greater granularity in terms of the identification of fee for service [54].

#### COVID-19

Due to the Coronavirus (COVID-19), remote contact with the study team will be privileged over face-to-face meetings (including trial visits), where possible, to ensure that both participants and staff are protected. Face-to-face trial visits that need to be performed will only be undertaken where care homes have been COVID-free for at least 14 days. Care homes (on behalf of the staff and residents) and researchers will be required to complete a COVID-19 screening tool prior to face-to-face visits to ensure risk is minimised. Visits will then be booked. During the visit, researchers will wear a mask and ensure social distancing and handwashing/hand sanitisation are performed, in line with local rules and national regulations. Before conducting any trial visits at the care home, the researchers will provide their details and a declaration of their own COVID status (no symptoms or contact with known COVID cases for 14 days). The provision of the details of the researchers will enable ‘track and trace’ to be performed, should this be necessary. Due to the sensitive patient population, every precaution will be taken to minimise the risk of infection, with decontamination taking place prior to entering and leaving the resident and the care home.

The number of confirmed cases of COVID19 within the care homes will be recorded at baseline, 6 months and 12 months to assess any impact the research may have had on the home during the study.

### Plans to promote participant retention and complete follow-up {18b}

The research team will have regular contact with the recruited care homes throughout the study period. Care homes will be kept informed of the study’s progress by the study team and via a quarterly email.

### Data management {19}

Information regarding how the data is to be collected, stored, and transferred will be included in the study-specific Data Management Plan. The study will be managed in accordance with General Data Protection Regulations, Good Clinical Practice (GCP) and relevant NWORTH Standard Operating Procedures (SOPs). Where data are stored locally at local sites, the study will adhere to the SOPs of the respective University.

The person-centred measures (questionnaires) will be collected on pre-printed case report forms (CRFs) for each resident. The symptoms checklist completed by care home staff on a weekly basis will be filed and locked in the care home manager’s office, ahead of collection by the local study team. Data from the paper CRFs will be transcribed onto a web-based CRF that will not include the participant’s name or other information that could identify them. The CRF will be considered the source data and should be consistent and verifiable with the information recorded on the study database.

All data will be stored securely on password-protected PCs/laptops and any paper records stored in locked drawers/filling cabinets in secure buildings. All participant personal information will be coded and anonymised at source. Participants will be allocated a unique study number, which will be used in any documentation associated with the study. Participants’ names will not appear on any documentation associated with the study apart from the Consent Forms, which will be kept separate in locked filing cabinets within the resident’s care home. Only members of the research team will have access to the data.

### Confidentiality {27}

Individual participant medical information obtained as a result of this study is considered confidential, and disclosure to third parties is prohibited with the exceptions noted below:CRFs will be labelled with a unique trial identification number.Medical information may be given to the participant’s medical team and all appropriate medical personnel responsible for the participant’s welfare.

NWORTH will preserve the confidentiality of participants taking part in the study, and the Sponsor is registered as a Data Controller with the Information Commissioners Office.

### Plans for collection, laboratory evaluation and storage of biological specimens for genetic or molecular analysis in this trial/future use {33}

Not applicable as no biological specimens will be collected as part of this trial.

